**Table 1 Tab1:**
[figure not shown]
Overview of the assessments

Note. S = screening; B (T1) = baseline assessment; T2 = 6–8 weeks after start of the treatment; T3 = 12–16 weeks after start of the treatment; F1 = 24 weeks after start of the treatment; F2 = 52 weeks after start of the treatment

*BDI-II* Beck Depression Inventory II; *CAPS-5* Clinician Administered PTSD Scale for DSM-5; *DAQ* Depressive Attributions Questionnaire; *DES-T* Dissociative Experiences Scale Taxon; *EMDR* eye movement desensitization and reprocessing; *EQ-5D-5L* 5-level EuroQol 5D version; *ImRs* imagery rescripting; *ITQ* International Trauma Questionnaire; *LEC-5* Life Events Checklist for DSM-5; *MHQoL-7D* Mental Health Quality of Life seven-dimensional Questionnaire; *PCL-5* PTSD Checklist for DSM-5; *PTCI* Posttraumatic Cognitions Inventory; *SCL-90-R H* Symptom Checklist-90-Revised Hostility subscale; *SCID-5-CV* Structured Clinical Interview for the DSM-5 Disorders-Clinician Version; *SCID-5-PD* Structured Clinical Interview for the DSM-5 Personality Disorders; *SECS* Self-Expression and Control Scale; *WHODAS 2.0* WHO Disability Assessment Schedule 2.0

^1^An additional assessment (waitlist assessment) is conducted if patients have a waitlist period of more than 5 weeks before the start of treatment

^2^Consisting of an assessment of the DSM-5 disorders, lifetime exposure to traumatic events, index trauma, traumatic memory, and encapsulated belief

^3^Extended with seven additional items. In addition to the standard assessments, the PCL-5 is also completed before every treatment session, starting with session 2

^4^A brief version of the semi-structured demographic interview including questions about the employment situation, medication use, substance use, and use of psychological treatments other than the study treatment

^5^This test for patients and therapists is assessed before the fourth and eighth treatment session

^6^These items are completed before every treatment session, starting with session 2, by the patient and therapist

Finally, the treatment sessions are videotaped. These recordings are used for supervision and adherence ratings. Within each country, a random sample of treatment sessions will be selected and rated for adherence by trained raters who are blind to condition. A subsample will be rated twice to assess the intraclass correlation coefficient (ICC). The recordings may also be used for secondary investigations (e.g., therapeutic alliance, exploration of effects of micro-techniques).

### Allocation

An independent staff member of the sponsor, not involved in the study, randomizes the patients per center to one of the four conditions (i.e., EMDR once a week, EMDR twice a week, ImRs once a week, or ImRs twice a week) using a computer-generated list. This list was created before the first patient was randomized based on block randomization (*N* = four or eight, with block size randomized) per center, and stratified by gender, to guarantee the balance between conditions per site and over time, and to control for the gender distribution. By randomly varying the block size, the unpredictability of the allocation sequence is enhanced. Only the independent staff member has access to the random list and will keep the list until the end of the research to ensure allocation concealment. The condition will be revealed to the patient with the invitation for the first treatment session (session frequency) and during the first treatment session (treatment type).

### Interventions

#### Format

Treatment consists of a maximum of 12 face-to-face sessions of 90 min. Based on the frequency condition the patient is allocated to, the treatment has a maximum duration of 8 weeks (twice-weekly frequency condition) or 16 weeks (once-weekly frequency condition). In the twice-weekly frequency condition, treatment sessions are offered twice a week with at least 1 day between the sessions. The time between sessions in the once-weekly frequency condition needs to be at least 6 days. Patients that have completed treatment before they reach the maximum of 12 sessions are allowed to complete treatment earlier, but the assessments are conducted at the originally planned assessment times. Early termination of treatment requires approval from the site investigators.

For both treatments, the first session involves scheduling the subsequent sessions (if not already done), introducing the treatment model, and constructing a list of trauma memories to be targeted during treatment. Patients in the ImRs condition receive a pilot rescripting of a minor, non-traumatic experience, to become familiar with the technique. Due to time constraints, there will be no pilot in the EMDR condition. In this condition, patients are prepared for trauma processing in the second session by doing the EMDR procedure preparation. In the subsequent sessions of both EMDR and ImRs, trauma processing of at least one traumatic memory is required in each session. The PCL-5, which will be completed by the patient before each session, can inform the patient and therapist about specific issues that should be addressed during the session (e.g., increase in guilt feelings). After each treatment session, therapists record the duration of the session and the number of traumas that were addressed during the session. Both treatments have been operationalized in treatment manuals.

#### EMDR

EMDR sessions are based on the eight phases of the EMDR standard protocol [14, 40]. The first session, as outlined above, incorporates Phases 1–3, namely history, preparation, and assessment. In addition to developing a list of traumatic experiences, the theory behind EMDR is explained, including describing the adaptive information processing model. A “safe place” is established, and the eye-tracking task is introduced. Based on a traumatic memory taken from the trauma list, the participants identify an image that represents the worst part of the memory. They are then supported to elicit a self-referential negative cognition associated with that image (for example, “I am a failure”). Following, the participant identifies a positive cognition to express what they would want to believe about him or herself when thinking of the image (for example, “I am worthwhile”).

Sessions 2–11 continue to follow Phases 4–8 of Shapiro’s standard protocol (desensitization, installation, body scan, closure, and reevaluation). At the beginning of each session, the participants are asked to comment on any intrusions experienced since the last session. They are then asked to return their focus to the memory that was discussed in the previous session. The participant is asked how the memory is recalled, including associated emotions, body sensations, and the subjective level of distress. Subjective distress is measured on a scale from 0 to 10; 10 being the highest level of disturbance and 0 the minimum. The participant also rates the validity of their positive belief when thinking about the traumatic memory. If the distress is two or less or if the same memory has been processed for two sessions, the therapist then chooses another memory from the trauma list. If not, the therapist continues with the standard EMDR protocol Phases 4–7 (i.e., desensitization, installation, body scan, and closure).

In Session 12 (or earlier if all disturbing memories are processed prior to this), the therapist is instructed to administer the future template. Accordingly, instead of focusing on a past memory, the participant selects a potential future situation that evokes distress, and this is then targeted to overcome any anticipatory anxiety or avoidant behavior.

#### ImRs

ImRs is delivered based on a modified version of the protocol developed by Arntz and Weertman [13]. In short, the therapist helps the patient to imagine a traumatic event and then a helping figure is introduced and changes the script to a better outcome where the needs of the traumatized person are met. Patients are instructed to describe the trauma in the first person, from the point of view of the child, in the present tense. They are guided to identify all sensory information (i.e., what they see, hear, feel, and smell), as well as their thoughts, feelings, and needs. When the traumatic memory and the associated emotions are sufficiently activated, the therapist will move to the rescripting part and introduce the helping figure. Thus, patients do not have to experience the whole trauma with its “hot spot”. In the first six sessions, the therapist is introduced as a helping figure, accompanies the child in the image and intervenes to stop the threat. The therapist turns to the child to ensure that the child’s needs are met (e.g., by comforting, reassurance, or reattribution). In Sessions 7–12, the patient’s adult self enters the image and then rescripts the scenario reporting it from the adult point of view. This is then repeated from the child’s point of view, allowing the child to experience to be protected and cared for by the adult self as well as to ask for any additional support required to ensure its needs are met. Trauma memories are “rescripted” until the patient is satisfied.

#### Therapists, training, and supervision

All therapists in this study are psychologists, psychotherapists, or psychiatrists trained in ImRs, EMDR, or both treatment types. In order to participate, EMDR therapists must have completed a level 1 basic training in EMDR and ImRs therapists were required to complete a basic training course in cognitive behavioral therapy (CBT). In addition, all therapists must have completed an additional 2-day training in EMDR or ImRs for PTSD related to childhood trauma focusing on the treatment protocols as investigated in the study.

Before therapists can start with the treatment, they are required to demonstrate their competence to deliver the treatment with pilot patients. These pilot treatments are evaluated during peer supervision and by the site investigator of the center. During the study, therapists are obliged to attend weekly peer supervision or supervision by an EMDR or ImRs supervisor at their site. Moreover, therapists and site supervisors can consult an expert for questions regarding EMDR ([name]) and ImRs ([name]). Treatment recordings can be used for supervision. In addition, treatment recordings are also assessed for treatment integrity using adherence scales (EMDR: modified EMDR Therapy Fidelity Rating Scale [41], and ImRs: ImRs Therapist Adherence and Competence Scale [42]).

#### Ancillary and post-trial care

In case of acute crisis during the study, patients may alter their medication or engage in another form of psychological treatment in addition to the study treatment. This will not lead to exclusion from the study. Details of medication use and other psychological treatments next to the study treatment will be recorded.

Following the assessment at 24 weeks after start of the treatment, the therapist will see the patient for an evaluation to determine if more treatment is needed. The type, intensity, and frequency of a potential further treatment will be determined based on the needs of the patient and the possibilities of the center. Details of any further treatment will be recorded. Note that further treatment might focus on other problems than PTSD.

### Coronavirus disease (COVID-19) pandemic

This study is being conducted during the coronavirus disease pandemic. As a consequence of this pandemic, face-to-face treatments can be restricted in mental healthcare centers depending on government and healthcare center policy. Patients who started treatment before the restrictions were executed will receive the remaining treatment sessions via videoconferencing, have a treatment pause, or discontinue with treatment because of no possibilities for videoconferencing. These patients will be excluded from the study as we will only include patients who received treatment face-to-face, so as not to introduce a confounding variable. The treatment will be postponed for patients for whom the treatment had not started or who had received only one treatment session. Treatment will be resumed when face-to-face treatment is permitted again, possibly with the use of a plexiglass barrier between the patient and therapist. These patients will be included in the study. Assessments will be conducted via phone or videoconferencing, and questionnaires will be completed by participants at home if face-to-face assessments are not allowed.

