After the screening assessments are completed, a final check of the inclusion and exclusion criteria is performed by the junior investigator and the patient is randomized by an independent staff member of the sponsor. After randomization, the site investigator of the center is informed of the patient’s allocated treatment condition and searches for a suitable therapist, taking into account the availability of the patient and the preference of the patient for a male or female therapist. At the same time, the baseline assessment (T1) is administered by a research assistant blinded to the patient’s allocated condition. If the time between the start of the treatment and the baseline assessment is more than 5 weeks, an additional assessment (i.e., waitlist assessment) is conducted before the patient starts with the treatment. After the baseline assessment (and, if applicable, the waitlist assessment) is completed and a therapist has been found, the patient starts the treatment. The session frequency of the treatment (i.e., twice a week or once a week) will be revealed to the patient with the invitation for the first session, but the treatment type (i.e., EMDR or ImRs) is not communicated to the patient until the first treatment session.

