### Statistical analyses

The statistical analyses will be performed according to the intention-to-treat principle. Change in the primary and secondary outcome measures and the relative effectiveness of the two frequency conditions (twice-weekly frequency condition versus once-weekly frequency condition) will be analyzed using mixed regression analyses. By using mixed regression analysis, all available data will be used, and dependencies among observations nested within individuals will be taken into account. Appropriate forms of the mixed regression models will be selected, based on the variable type (e.g., scale, count, dichotomous) and taking into account the distribution of the residuals. To assess the comparative effectiveness of EMDR and ImRs and whether treatment type moderates the effect of session frequency, additional terms will be added to the model. In addition to the primary analyses based on the intention-to-treat principle, a completers analysis focused on the change in the primary outcome measure will be conducted by excluding patients who discontinued treatment or deviated from the protocol (e.g., duration of more than 16 weeks in the once-weekly frequency condition, other psychological treatment next to the study treatment, unstable level of medication during the treatment period). No interim analyses are planned. Finally, to examine underlying change mechanisms of session frequency (i.e., memory and learning, therapeutic alliance, motivation, and reluctance and avoidance), advanced mediation analysis will be performed (e.g., mixed regression for Granger Causality models [118]).

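### The COVID-19 rule excludes randomised patients caught mid-treatment, which contradicts intention-to-treat and is expected to remove more once-weekly than twice-weekly patients

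*Protocol article*

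**What the plan says.** All references are to the protocol article.

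- **Statistical analyses:** "The statistical analyses will be performed according to the intention-to-treat principle". Removing patients who discontinued or deviated is reserved for a separate completers analysis.
- **Coronavirus disease (COVID-19) pandemic:** "Patients who started treatment before the restrictions were executed will receive the remaining treatment sessions via videoconferencing, have a treatment pause, or discontinue" where videoconferencing is impossible. The next sentence reads: "These patients will be excluded from the study as we will only include patients who received treatment face-to-face". The reason given is to avoid a confounder. For the others: "The treatment will be postponed for patients for whom the treatment had not started or who had received only one treatment session", and these patients stay in the study.
- **Procedure:** after screening, "the patient is randomized by an independent staff member of the sponsor", and treatment starts later. Anyone in treatment is therefore already randomised. Patients who stop treatment or deviate are encouraged to continue assessments.
- **Ancillary and post-trial care:** a medication change or additional psychological treatment in an acute crisis does not lead to exclusion.
- **Format:** "Treatment consists of a maximum of 12 face-to-face sessions of 90 min", within at most 8 weeks (twice-weekly) or 16 weeks (once-weekly). Patients who have completed treatment before 12 sessions may finish early, with site-investigator approval.

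**The concern.** A patient cannot be analysed as randomised and also be removed from the study for what happened during treatment. The text excludes these patients from the study itself, not from one analysis set, so the conflict is not a detail left to an analysis plan.

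The rule is also not neutral between the arms. A patient is at risk of exclusion from the second session to the last. The length of that window is set largely by session frequency, which is the factor the trial tests. Within an arm, it is shortened for patients who finish early or drop out. The primary comparison would then be between groups selected after randomisation, partly by arm and partly by treatment course.

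**Working it through.** **1. The plan's own power figure.** Two-sample t-test, two-sided 0.05, 100 per frequency group: d = 0.50 gives 94.0% (stated 94%) and d = 0.40 gives 80.4% (stated 80%). Both reproduce.

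**2. Length of the exclusion window.** Sessions 2 to 12 span ten gaps.

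- Nominal pace: 10 × 1 = 10 weeks once-weekly and 10 × 0.5 = 5 weeks twice-weekly. Ratio 2.0.
- Maximum duration, evenly spaced (10 of 11 gaps): 16 × 10/11 = 14.5 and 8 × 10/11 = 7.3 weeks. Ratio 2.0.
- Maximum duration with the first gap at nominal length: 16 − 1 = 15 and 8 − 0.5 = 7.5 weeks. Ratio 2.0.
- Once-weekly at its fastest ("The time between sessions in the once-weekly frequency condition needs to be at least 6 days"), twice-weekly at maximum: 60/7 = 8.6 against 7.3 weeks. Ratio 1.2.
- Once-weekly at maximum, twice-weekly at nominal pace: 15 against 5 weeks. Ratio 3.0.

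Allocation is equal and blocked for balance over time, so start rates should be similar in the arms. The expected ratio of removals is then the ratio of the windows.

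**3. Expected number removed by one restriction.** Number = start rate × window. The article gives no accrual curve, so I assume even accrual of 220 patients and all sites restricting together. June 2018 to April 2022 is 46 months. Subtracting one year of follow-up leaves 34. Thirty months is taken as a lower assumption. Rate per frequency group = 220 / (months × 4.345) / 2.

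| Accrual | Rate per week | Once-weekly (10–15 wk) | Twice-weekly (5–7.5 wk) | Total |
|---|---|---|---|---|
| 30 months | 0.844 | 8.4–12.7 | 4.2–6.3 | 12.7–19.0 |
| 34 months | 0.745 | 7.4–11.2 | 3.7–5.6 | 11.2–16.8 |
| 46 months | 0.550 | 5.5–8.3 | 2.8–4.1 | 8.3–12.4 |

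The overall range is about 8 to 19 patients.

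**4. Power after removal.** Taking patients 2:1 from 200 analysable patients: with 10 removed, power is 92.9% (d = 0.50) and 78.3% (d = 0.40). With 20 removed it is 91.5% and 76.0%.

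**5. Possible size of the bias.** The article gives no early-completion rate, so these cases are illustrative. Each arm starts with 110 patients, and fast responders are assumed to do 1 SD better. The bias in SD units is the difference between arms in the share of fast responders left.

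- *Mild:* 20% are fast and have half the window; 34-month accrual; windows 10 and 5 weeks. Once-weekly: (22 − 0.745)/(110 − 6.70) = 0.2058. Twice-weekly: (22 − 0.372)/(110 − 3.35) = 0.2028. Difference 0.003 SD.
- *Harsh:* 50% are fast and never caught; 30-month accrual; windows 15 and 7.5 weeks. 55/(110 − 6.33) = 0.5305 and 55/(110 − 3.16) = 0.5148. Difference 0.016 SD.
- *Harsh, three all-site restrictions:* 55/(110 − 18.99) = 0.604 and 55/(110 − 9.49) = 0.547. Difference about 0.06 SD.

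These cases let only fast responders escape. Patients who dropped out before a restriction also escape, and would act the other way if their outcomes are worse.

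**The case against.** The strongest reply is that the trigger is external: government and centre policy. If every patient used the full schedule, removal would depend only on arm and start date. Unequal numbers alone would then leave the comparison essentially unbiased. That stands, so the imbalance by itself does not prove bias. It does not answer the whole point. The restriction date is external, but still being in treatment on that date is not, because early completion is allowed and earlier dropouts fall outside the rule. Nor does it remove the conflict with intention-to-treat.

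A reader might infer more than the documents support:

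- *That the once-weekly arm loses slow responders, so the direction of bias is known.* Early completers and earlier dropouts both escape, and the article gives no figures for their net effect.
- *That the split is fixed at 2:1.* It is an expectation. With only 10 removals split at 2/3, the chance that the once-weekly arm loses more is about 79%.
- *That each restriction removes the full counts above.* Those assume that all eleven centres in three countries restrict together, whereas the article says restrictions depend on government and centre policy.
- *That power is seriously damaged.* It is not: the loss at d = 0.50 is about 1 to 2.5 percentage points for 10 to 20 removals.

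**Conclusion.** The contradiction is explicit and nothing else in the article reconciles it: the COVID-19 section removes randomised patients whom the intention-to-treat principle keeps, while comparable deviators stay in the study. Removal is expected to be more frequent in the once-weekly arm under similar start rates, and it depends on treatment course, so the primary comparison would no longer be between the groups as randomised.

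The direction of bias is undetermined. Its size is probably small: from 0.003 to about 0.06 SD in the illustrative cases, against the d = 0.40 to 0.50 the trial is powered for. The case for change rests on the broken randomised comparison and the conflict in the text, not on a large numerical effect. It is also a matter of timing: if exclusion also ends assessment, which the text leaves open, those outcomes cannot be recovered later. Replacing the excluded patients would restore the number but not the comparison.

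**What to change.** Amend the COVID-19 section so that every randomised patient stays in the primary intention-to-treat analysis, whatever the mode or completion of treatment, and continues assessments. The section already provides for assessment by phone or video.

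Make the face-to-face-only set a sensitivity analysis, and say that it is selected after randomisation. A rule on treatment start date, identical in both arms, is preferable, but its loss should be stated. For example, dropping everyone who started within 16 weeks before an all-site restriction would remove about 0.745 × 16 × 2 = 24 patients at 34-month accrual. That is more than the present rule removes, and would include some treated entirely face-to-face.

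The cost is one amendment and continued assessment of patients already enrolled. The downside is that some videoconference, paused or interrupted treatments enter the primary analysis. The sensitivity analysis shows how much that matters.
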